Although superior to dialysis treatment, kidney transplantation involves the inherent risk of rejection and/or graft failure that incurs costly hospitalizations, laboratory tests and anti-rejection treatments that are associated with poor patient outcomes [3, 10–14]. To minimize the risk of rejection, recipient patients are placed on lifelong regimens of immunosuppressive drug treatments [15] and are monitored for signs of rejection [3]. A combination of two or three different immunosuppressants are taken on a long-term basis to prevent rejection. However, as with all medications, patients may experience adverse reactions and these may include an increased risk of infections, diabetes, increased susceptibility to certain cancers, increased blood pressure and weight gain [12]. It is also true that the immunosuppression process can increase the risk of comorbidities. Despite the nuances of the medication, adherence to the immunosuppressant regimen is vital to providing the grafted kidney with the best chance of survival and function after kidney transplantation [6]. Graft survival after kidney transplantation emphasizes adherence to immunosuppressive therapy, [11, 12, 16] as well as adherence to other prescribed medications, which are important to ensure control of the comorbidities that commonly accompany patients with end-stage CKD and thus not compromising the health of the patient and the transplanted kidney [7].

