However, despite a long and frustrating time on the waiting list following a successful transplant, many patients develop problems with adherence to their immunosuppressive medications [7, 16]. Not taking prescribed immunosuppressive drugs (defined as taking drugs <95.1% of days) is associated with a 60% increased risk of kidney transplant failure and premature death [11, 17]. Adherence in this context refers to the “extent to which the patient’s behavior matches agreed prescriber recommendations” [6], and non-adherence (NA) as “deviation from the prescribed drug regimen sufficient to negatively influence the effect” [18]. In a broader context, adherence is defined by the World Health Organization as “the extent to which a person’s behavior–taking medication, following a diet and/or carrying out lifestyle changes–corresponds to the agreed recommendations of a health professional” [19]. Non-adherence to immunosuppressive medication is an important risk factor for unfavorable post-transplant clinical outcomes, reducing patient survival and causing waste of health resources [20]. However, it remains a common problem in this patient population and has been identified as the second common cause of late graft failure in kidney transplant patients. In 2011, Suárez et al. [21] estimated that the non-adherence rate is between 20% and 54% and that the lack of compliance can contribute to 20% and 16% of graft loss. A recent meta-analysis revealed that the magnitude of NA for immunosuppressants in kidney transplant recipients was as high as 35.6 cases per 100 patient-years. The incidence of NA among kidney transplant recipients was significantly higher than that of the general population of solid organ transplant recipients, which was 22.6 cases per 100 patient-years. That study estimated that 15% to 60% of late acute rejections and 5% to 36% of graft losses were associated with NA in kidney transplant patients [18, 22].

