
The following study visits, at months 6 and 12 post-transplant, will be for evaluation of predictive validity. Predictive validity, the second component of criterion validity, is the ability of a questionnaire score to predict a future outcome, as expected by theory, which represents the criterion or gold standard. The main difference to concurrent validity is that in predictive validity the criterion is measured at a later time than the scale scores, while in concurrent validity both are measured at the same time. In this case, the criterion is obviously medication non-adherence. However, there is no single method for measurement of medication non-adherence that can be considered a gold standard. Methods for measurement of medication non-adherence may be divided into objective methods, including pill count, pharmacy refill records, serum level of immunosuppressants, and electronic monitoring of opening of pill bottles, and subjective methods, such as medication adherence scales, patient self-reporting, and physician impressions. A combination of methods is usually adopted in the evaluation of medication non-adherence to immunosuppressants and, in keeping with this approach, we will use three methods that independently discriminate medication adherent from non-adherent patients: patient self-report of non-adherence using the Morisky Green Levine Medication Assessment Questionnaire (MGL MAQ) [30], the trough serum levels (C_0_ levels) of immunosuppressants measured at the study visits, and reports on pharmacy refill of immunosuppressants. The MGL MAQ tool consists of four questions with a yes/no answer, two being about forgetfulness on taking medication, and two on behavior on taking medication. Patients will also be classified as medication non-adherents if trough serum levels of immunosuppressants measured at each 6- and 12-months study visit are lower than 4 ng/mL for tacrolimus [31], 4 ng/mL for sirolimus [32], 3 ng/mL for everolimus [33], and 50 ng/mL for ciclosporin [34]. All participating healthcare centers belong to the National Health System, which delivers immunosuppressant medication without costs to patients at a central pharmacy, making pharmacy refill records easily accessible for identification of patients who fail to get their medication and who will be considered, in this study, as medication non-adherents. A patient will be considered as non-adherent if being classified as non-adherent by any of the three methods at either the 6-month or the 12-month visit.

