### Sample sizes

For the focus group, eight patients will be selected, which is within the recommended size for focus groups [37]. For the cognitive interviews, sample size will be determined by saturation, that is, when no new information is obtained from participants, but it expected to require no more than 10 patients. For the development of questionnaires measuring a latent construct using factor analysis, and for reliability assessment, there are neither theoretical foundations, nor formal methods of estimation of the required sample size, and the required numbers are based on rules of thumb suggested by several authors, with some recommending a sample size defined by a ratio of participants for each scale item, often 10:1 [38], while others propose a fixed number of participants, independent of the number of items, most commonly in the range of 200 to 300 subjects [39–42]. Accordingly, the sample size for this part of the study will be no less than 300 patients. For the test-retest reliability analysis, a sample size of 20 subjects would be sufficient to ensure 80% power with an alpha error of 0.05 to identify a correlation greater than 0.60, however such small sample will not provide adequate robustness to the results, so a minimum sample size of 60 patients was defined.

The sample size for the external validity study is determined by the requirements for the evaluation of the predictive validity of the KATITA questionnaire. Assuming that the area under the ROC curve (AUROC) of the questionnaire in the prediction of immunosuppressive medication non-adherence would be at least 0.75, and that the proportion of non-adherent patients in the first 12 months after transplant will be about 50%, a sample of 364 patients would estimate the AUROC with an error of ±0.10 with 95% confidence [43]. The same sample size will be used in confirmatory factor analysis for assessment of structural validity of the factorial model, scale sensitivity to change, and concurrent validity assessment.

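### The trough criterion for non-adherence uses one fixed floor per drug and ignores the prescribed regimen, which conflicts with the protocol's own definition of adherence

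*Protocol article*

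**What the plan says.** The External validity section builds the criterion for predictive validity from three methods: self-report, trough level and pharmacy refill.

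- **Trough.** A patient counts as non-adherent if "trough serum levels of immunosuppressants measured at each 6- and 12-months study visit are lower than 4 ng/mL for tacrolimus". Sirolimus, everolimus and ciclosporin each have their own single floor (4, 3 and 50 ng/mL). The prescribed dose, the prescribed target and prescriber-ordered changes are not mentioned.
- **Refill.** Pharmacy records serve for "identification of patients who fail to get their medication and who will be considered, in this study, as medication non-adherents".
- **Combination.** The final label is non-adherent if the patient is "classified as non-adherent by any of the three methods at either the 6-month or the 12-month visit".

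The Introduction defines the construct differently. Adherence is the extent to which the patient's "behavior matches agreed prescriber recommendations", and non-adherence is "deviation from the prescribed drug regimen sufficient to negatively influence the effect". Both definitions take the prescription as the reference.

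Under External validity assessment, the AUROC, sensitivity, specificity and both predictive values are computed for pre-transplant KATITA scores. The Sample sizes section says that predictive validity sets the size of the external study, on the assumption that the AUROC "would be at least 0.75" and that about half of patients are non-adherent.

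**The concern.** A low trough can come from the patient's behaviour or from the prescriber's order. The Introduction counts only the first as non-adherence. The trough rule cannot tell them apart, and because any one method at either visit decides the label, normal self-report and complete refills do not rescue a patient who took a reduced regimen exactly as ordered.

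A questionnaire given before transplant cannot be expected to foresee later prescribing decisions. To the extent that the criterion records those decisions, KATITA is judged against something it was not built to predict, and every predictive-validity statistic inherits the error. The article fixes the floors, the visits and the combination rule itself, so this is a stated rule and not a detail left open.

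**Working it through.** **1. The two definitions applied to one patient.** The prescriber reduces or holds a monitored drug, the patient complies, and the month-6 trough is below the floor.

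- Introduction: behaviour matches the recommendation, so the patient is adherent.
- External validity: the trough is below the floor at one visit, so the patient is non-adherent, whatever the other two methods show.

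The labels contradict each other for the same facts.

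**2. Inputs.**

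- True AUROC A = 0.75 and true non-adherence p = 50% (Sample sizes).
- Lower values of p for comparison: 20%, the lower end of the range cited in the Introduction, and 35% (assumed).
- f = share of truly adherent patients mislabelled through prescriber-driven low troughs. The documents give no figure. **Assumed** range: 5%, 10%, 20%.
- **Assumed**: mislabelling is unrelated to the KATITA score.

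**3. Effect on the AUROC.** Among those labelled non-adherent, the share truly non-adherent is w = p / (p + (1 − p)f). Mislabelled patients score like adherent ones, so they contribute 0.5:

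observed AUROC = 0.5 + (A − 0.5) × w

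At p = 0.50:

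- f = 5%: w = 0.50/0.525 = 0.952; AUROC = 0.5 + 0.25 × 0.952 = 0.738
- f = 10%: w = 0.50/0.55 = 0.909; AUROC = 0.727
- f = 20%: w = 0.50/0.60 = 0.833; AUROC = 0.708

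| True non-adherence | f = 5% | f = 10% | f = 20% |
|---|---|---|---|
| 50% (plan) | 0.738 | 0.727 | 0.708 |
| 35% | 0.729 | 0.711 | 0.682 |
| 20% | 0.708 | 0.679 | 0.639 |

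A simulation at p = 35.6%, f = 15% gave 0.696, against 0.697 by the formula.

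If the plan's 50% is instead read as the proportion *labelled* non-adherent, and 5%, 10% or 20% of those are false labels, the AUROC is 0.5 + 0.25 × (0.95, 0.90, 0.80) = 0.738, 0.725 or 0.700.

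**4. Effect on the other statistics** at any fixed cut-off, under the same assumption:

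- Specificity: those still labelled adherent are a random subset of the truly adherent, so it is unchanged in expectation.
- Sensitivity becomes w × sensitivity + (1 − w) × (1 − specificity). It falls whenever the score discriminates at all.
- Positive predictive value becomes PPV + (1 − PPV)f. It rises, but only against the faulty label.
- Negative predictive value becomes NPV × (1 − f). It falls.

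**5. Either-visit rule.** Here f is the error accumulated over two visits. If the per-visit error is 5% and visits are independent (both assumed), f = 1 − 0.95² = 9.75%. At 10% per visit, f = 1 − 0.90² = 19%.

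**6. Comparison with the planned precision.** The Hanley–McNeil variance with 182 patients per group and A = 0.75 is [A(1 − A) + 181(A/(2 − A) − A²) + 181(2A²/(1 + A) − A²)] / 182² = (0.1875 + 6.7875 + 14.5446)/33124 = 0.000650. The standard error is 0.0255 and the 95% half-width is 1.96 × 0.0255 = 0.050. The article states ±0.10 for 364 patients; that mismatch is a separate matter. At the plan's 50% true non-adherence, the falls of 0.012, 0.023 and 0.042 lie within either half-width.

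**The case against.** The strongest reply has four parts.

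- **No method is a gold standard.** The article says so and combines three methods for that reason. The Introduction's definition of non-adherence also refers to loss of effect, which a low-exposure floor can be seen as trying to capture. This explains why a trough is used. It does not remove the conflict, because that definition still requires a departure from what was prescribed, and the any-one-method rule lets the trough decide alone.
- **The size is assumed and modest.** This stands. The documents contain no rate for prescriber-driven low troughs, and at the plan's 50% true non-adherence the illustrated falls are within sampling error. A fall of this kind is nevertheless systematic, and more patients would not reduce it.
- **Refills, switches and withdrawals.** A reader might infer that a drug the prescriber stopped would count as a missed refill and a low trough together. The text does not support this. Refill concerns patients failing to get *their* medication, which most naturally means what is currently prescribed. The floors are drug-specific, so a converted patient would naturally be judged on the new drug. What can be said is that the text does not spell this out.
- **Two monitored drugs.** A reader might also infer that many patients must clear two floors per visit, since the Introduction says "A combination of two or three different immunosuppressants are taken on a long-term basis to prevent rejection". It does not say that two of the four drugs with floors are combined, so no figure can be built on it.

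A patient on none of the four drugs cannot fail the trough test, but self-report and refill can still detect non-adherence. That is a reason to combine methods and not an error in the rule.

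**Conclusion.** The concern holds for the trough component. As written, it labels as non-adherent a patient who follows a prescriber-ordered reduction or hold that takes the level below the floor, contrary to the Introduction's definition. That label is the criterion for the external study's predictive claim.

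If the mislabelling is unrelated to KATITA, the result is attenuation: a true AUROC of 0.75 at 50% true non-adherence falls to between 0.738 and 0.708 for assumed mislabelling of 5% to 20% of adherent patients, and further at lower true non-adherence. These figures illustrate the mechanism and do not estimate its size. If mislabelling is related to the score, the direction of bias is open.

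A reader might infer that specificity is biased too. Under random mislabelling it is not, in expectation. The documents also do not show that the bias differs by centre, or that prescribed targets lie below the floors.

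**What to change.** Reconcile the trough rule in External validity with the definitions in the Introduction:

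1. At months 6 and 12, record from the chart the regimen and target in force and any prescriber-ordered reduction, hold, switch or stop.
2. Judge the trough component against that regimen. Where a prescriber-ordered change explains a low level, mark the component not evaluable.
3. State that refill is judged only on medication currently prescribed.
4. Fix these rules before outcomes are classified, and have the classification done without sight of KATITA scores.
5. Keep the fixed-floor label as a sensitivity analysis.

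The cost is a few chart fields at two existing visits and a reworded outcome definition. These are ordinary chart items, so they fit the commitment under Objectives to collect only what routine care needs. No extra test or patient is required. The downside is that some patients will have fewer evaluable components. No clinical threshold is proposed.

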#### Item pool development

Once the construct is clearly identified, based on the definitions of medication non-adherence presented above, the first step in scale development will be item generation, the identification of the appropriate questionnaire questions, which will combine a deductive and an inductive method. The former will consist of a search for medication adherence scales from bibliographic databases. Statements from those scales related to patients’ medication-taking behaviors, to barriers to good medication-taking behavior, or to beliefs associated with medication adherence will be selected for inclusion in a preliminary item pool of potential statements for the KATITA scale. The inductive method will consist of a focus group of consecutive patients attending the nephrology clinic of the coordinating center, of both sexes, over 18-years-old, who are in the kidney transplant waiting list, moderated by a psychologist experienced in kidney transplant patients. The patients will be asked to review and reformulate or rephrase the previous selected items, and add new ones reflecting their experiences and thoughts on medication taking. The focus group sessions duration should not exceed 60 minutes and will be repeated until saturation occurs, that is, when no additional concepts are elicited in two consecutive sessions. The focus group sessions will be recorded and the transcripts will be reviewed by the study investigators, who will select all the statements that may reflect patients’ attitudes, behaviors, beliefs and barriers to medication adherence.

The next task will be the assessment of content validity by a panel of three clinical pharmacists with extensive experience in the pharmaceutical care of kidney transplant patients. These expert judges, based on their experience in interactions with this population during pharmacotherapeutic consultations, will independently review each item to decide, through consensus, whether it should be eliminated due to irrelevancy or unrelatedness to medication non-adherence. The panel will also review the wording of each item for complexity and ambiguity, and may generate new questionnaire items.

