#### External validity assessment

For the analysis of the scale sensitivity to change, the time interval between baseline and transplantation will be presented by the median and interquartile range, and the change will be tested with the Wilcoxon signed rank test comparing baseline to 3-month scores. The magnitude of the change will be interpreted using the standardized response mean (SRM), which is the mean difference between baseline and 3-month post-transplant scores divided by its standard deviation [48], as moderate if SRM>0.5, or large if SRM>0.8. For the evaluation of concurrent validity, Spearman’s rho will be used to estimate the correlation between KATITA scores and the scores of the BAASIS and the CEAP-VIH scales, and the Wilcoxon-Mann-Whitney ranksum test will be used to test the difference in KATITA scores between adherent and non-adherent according to BAASIS. For the evaluation of the predictive validity of the KATITA questionnaire, the AUROC, sensitivity, specificity, positive predictive value and negative predictive value, and corresponding 95% confidence intervals, will be computed for pre-transplant KATITA scores. Structural equation modeling will be used for confirmatory factor analysis, with goodness of fit evaluated with the chi-square test/degrees of freedom statistic, Root Mean Square Error of Approximation (RMSEA), Comparative Fit Index (CFI), Tucker-Lewis index, standardized root mean squared residual and coefficient of determination.

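### The any-positive non-adherence criterion mixes self-report with objective methods, so its AUROC alone cannot show whether KATITA predicts objectively measured non-adherence

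*Protocol article*

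**What the plan says.** The External validity section of the protocol concedes that "there is no single method for measurement of medication non-adherence that can be considered a gold standard". It then says "we will use three methods that independently discriminate medication adherent from non-adherent patients": the MGL MAQ, trough levels and pharmacy refill records. The MGL MAQ has four yes/no questions, "two being about forgetfulness on taking medication, and two on behavior on taking medication". A trough result counts when "trough serum levels of immunosuppressants measured at each 6- and 12-months study visit are lower than" a fixed value for each drug. The three methods are merged into one binary criterion: a patient is "non-adherent if being classified as non-adherent by any of the three methods at either the 6-month or the 12-month visit".

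Under External validity assessment, the pre-transplant KATITA score is evaluated by "the AUROC, sensitivity, specificity, positive predictive value and negative predictive value", with 95% confidence intervals. The text does not separate self-report from the objective methods. Under Sample sizes, 364 patients are planned for an AUROC of at least 0.75 with about 50% non-adherent.

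Under Item pool development, part of the KATITA pool comes from published adherence scales: "Statements from those scales related to patients’ medication-taking behaviors" are among the material to be selected. Focus groups and an expert panel then revise the pool and add to it.

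**The concern.** Three imperfect methods at two visits give six chances to be labelled non-adherent, and one positive is enough. False positives therefore accumulate. If they are unrelated to the KATITA score, the AUROC against the composite falls below the AUROC against true non-adherence.

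A second pull runs the other way. KATITA is self-rated and one component of the criterion is a self-report on medication-taking. A patient's tendency to admit or deny lapses can affect both, so part of the apparent prediction may be shared response style.

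This AUROC determines the size of the external study and is its evidence of predictive validity. A moderate value could reflect a good scale judged against a noisy criterion. A good value could reflect agreement between two questionnaires. The composite figure alone cannot tell these apart, and sensitivity, specificity, PPV and NPV rest on the same labels.

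**Working it through.** **The plan's own figure.** Hanley-McNeil variance with A = 0.75: Q1 = A/(2−A) = 0.600, Q2 = 2A²/(1+A) = 0.643, and Var = [A(1−A) + (n1−1)(Q1−A²) + (n2−1)(Q2−A²)]/(n1·n2). With n1 = n2 = 182, SE = 0.0255 and the 95% half-width is 0.050. So 364 is reproduced when the total interval width is 0.10; a literal ±0.10 would need about 92. That is a separate matter. The question here is whether the criterion is valid, not whether the sample is large enough.

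**Downward pull.** The protocol gives no error rates, so these inputs are assumptions: true non-adherence p = 0.30, true AUROC 0.80, per-test sensitivity 0.5, per-test false-positive rate f of 2%, 5% or 10%, errors independent and unrelated to the score.

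- Composite sensitivity: 1 − 0.5⁶ = 0.984.
- Adherent patients mislabelled: F = 1 − (1−f)⁶.
- Composite prevalence: q = 0.30 × 0.984 + 0.70 × F.
- Predictive values of the composite label for the truth: PPV = 0.295/q, NPV = 0.70(1−F)/(1−q).
- Observed AUROC = 0.5 + (0.80 − 0.5)(PPV + NPV − 1).

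| f | F | q | PPV | NPV | Observed AUROC |
|---|---|---|---|---|---|
| 2% | 11.4% | 37.5% | 0.79 | 0.99 | 0.73 |
| 5% | 26.5% | 48.1% | 0.61 | 0.99 | 0.68 |
| 10% | 46.9% | 62.3% | 0.47 | 0.99 | 0.64 |

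**Dependence.** Six independent errors is the extreme case.

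- If the second visit adds nothing (three independent tests, sensitivity 1 − 0.5³ = 0.875), the same formula gives 0.74, 0.70 and 0.65.
- If false positives are fully dependent, F is only 2%, 5% and 10%. With sensitivity held at 0.984 the AUROC is then 0.78, 0.77 and 0.74.

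**Upward pull.** A simulation of 400,000 patients per setting assumed a true AUROC of 0.75, true non-adherence of 35.6% (the figure per 100 patient-years in the Introduction, borrowed as a proportion), 95% detection, false positives per visit of 5% to 20% for self-report and 0% to 10% for each objective method.

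- Self-report error unrelated to KATITA: composite AUROC 0.62 to 0.70.
- Self-report error correlated 0.3 to 0.7 with KATITA: 0.66 to 0.85, so on either side of the true 0.75.

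In a second example KATITA has no relation to true adherence but shares a self-report factor with the criterion (loadings 0.3 to 0.5; positives 35% self-report, 15% trough, 10% refill). The composite AUROC is 0.55 to 0.58, against 0.50 for trough/refill only. The inflation is modest, but only the objective-only figure reveals it.

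**Requiring two of three methods.** Under the first set of inputs each method, positive at either visit, has sensitivity 1 − 0.5² = 0.75. Two of three gives 3(0.75²)(0.25) + 0.75³ = 0.84, against 0.98 for any-positive. The AUROC is 0.78, 0.76 and 0.72. Specificity improves at a visible cost in sensitivity.

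**Precision of an objective-only AUROC.** With N = 364 and AUROC 0.75, the Hanley-McNeil half-width is 0.050 at 50% positive, 0.063 at 25% and 0.078 at 15%. The last two shares are assumptions.

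**The case against.** The rule is deliberate and disclosed. The protocol says that no gold standard exists, says that combining methods is usual, and fixes the rule in advance. A sensitive criterion suits a preventive tool. The AUROC for the composite as defined is not biased; bias exists only relative to an unobserved truth. An earlier questionnaire predicting later reported behaviour is close to what predictive validity means, and the two instruments differ in format and timing. Analyses by method may stand in a fuller plan. All of this is fair, and it is why the composite should be kept and why missing component analyses are not in themselves the fault. It does not remove the limit on what one mixed AUROC can show.

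A reader might also infer more than the documents support:

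- **That KATITA shares items with the MGL MAQ.** The Introduction lists a MAQ among reviewed scales, and nothing under Item pool development excludes its statements. No text says that they enter the pool, which is also reworked and reduced before the final scale.
- **That the AUROC is known to be inflated, or known to be attenuated.** There are two opposing pulls and one net bias, whose sign is unknown.
- **That the planned 50% non-adherence is an artefact of mislabelling.** In the 5% example, 29.5 of the 48.1 points are true non-adherers, and the Introduction's range of 20% to 54% reaches 50% without any mislabelling.
- **That low troughs after a prescriber's change are being misclassified.** The protocol describes no such changes.

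**Conclusion.** The point holds as a limit on interpretation. Relative to true non-adherence, the any-positive rule loses specificity and pulls the AUROC toward 0.5, while shared self-report style may pull it up. The net direction cannot be determined from the protocol. If the errors are unrelated to KATITA, a true AUROC of 0.80 would appear as 0.64 to 0.73 with independent errors, and as 0.74 to 0.78 with fully dependent false positives and sensitivity held at 0.98. Correlated self-report error can take the composite above the truth. Every error rate here is an assumption, so these figures illustrate size and are not estimates for this study. The firm conclusion is that the composite AUROC alone cannot establish prediction of objectively measured non-adherence. The study design and sample size need not change on this account.

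**What to change.** Keep the any-positive composite as the main criterion. Pre-specify alongside it the AUROC with 95% CI (a) for each of the three methods separately and (b) for trough/refill only. Limit any claim that KATITA predicts objectively measured non-adherence to what (b) supports. Two-of-three agreement may be added as a sensitivity analysis, with its lower sensitivity stated; it is a trade-off and not a correction of the rule. Do not take MGL MAQ statements verbatim into the KATITA item pool.

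The added AUROCs use data already being collected. The cost is fewer positives and wider intervals for the objective-only criterion: a half-width of about 0.06 to 0.08 if 25% to 15% are positive, against 0.05 at 50%.
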